## Withdrawal of individual subject

Subjects can leave the study at any time for any reason if they wish to do so without any consequences. The investigator can decide to withdraw a subject from the study for urgent medical reasons.

### Specific criteria for withdrawal (if applicable)

In case a subject does not comply with the protocol it also can be decided to exclude that subject from further participation in the experiment.

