Several candidate gene polymorphisms involved in weight management are already identified. A well-known example is the single nucleotide polymorphism (SNP) rs993909 in the fat mass and obesity-associated (FTO) gene (4-8). The A allele is associated with increased body mass index (BMI) (6). It has been suggested that FTO influences adiposity by affecting appetite. Indeed, the TA/AA genotype predisposes individuals to a reduced postprandial response in hunger and satiety (4). The Pro12Ala polymorphism of the peroxisome proliferators-activated receptor gamma 2 (PPAR2) is also strongly associated with weight management and specifically with weight maintenance (2, 3). The frequency distribution for the PPAR2 genotypes is different between subjects successful in weight maintenance after weight loss and subjects unsuccessful in weight maintenance after weight loss (9), with less heterozygous individuals in the successful group compared to the whole group. Weight regain was significantly greater in women with the Ala12 allele than women homozygous for the Pro12 allele (9, 10). The susceptibility towards weight regain in the Ala12 carriers might be due to decreased fat oxidation. Another polymorphism that shows specific associations with weight maintenance is the Arg16Gly polymorphism in the beta 2 adrenoreceptor (ADRB2) gene (2, 3). Individuals with weight regain more frequently had the Gly16 allele for the ADRB2 polymorphism compared to subjects who exhibited 24-month maintenance of weight loss (11). Polymorphism in the perilipin (PLIN) gene has also been associated with weight management, although women seem to be more sensitive to the genetic effects of perilipin than men (2, 3, 12). Obese patients carrying the 11482A allele have shown to be resistant to one-year weight management programme with a low-energy diet (13). Polymorphisms in the uncoupling proteins (UCPs) have been shown to influence exercise efficiency, resting energy expenditure (REE), substrate oxidation and body weight change. For example, the A3826G polymorphism in the UCP1 gene has been linked to lower weight loss response to a 25% reduction in energy intake, in which GG homozygotes were more resistant to weight loss (14). For the beta 3 adrenoreceptor (ADRB3) Trp64Arg polymorphism carriers of the Arg64 allele have shown to be more resistant to weight loss (2, 3). Other polymorphisms have been associated with biological or behavioural factors involved in weight management, like the AG/GG carriers in rs2267668 and AC/CC carriers in rs2076168 of the PPAR gene showed less physical activity than the AA carriers (15). The rs8192678 SNP in PPAR co-activator 1 (PPARC1) was also associated with physical activity, with GA/AA carriers spending more time on high-intensity physical activity than GG carriers (15). Certain SNPs have been shown to influence postprandial responses. Like the postprandial response in plasma ghrelin levels have been associated with SNPs in peptide YY (PYY) gene (215G>C) and the leptin receptor (LEPR) gene (326A>G and 688A>G), and in plasma PYY levels with SNPs in LEPR gene (668A>G) and neuro-peptide Y 2 receptor (NPY2R) gene (585T>C) (16). Also dietary restraint and disinhibition were associated with a SNP (477G>A) in the ghrelin receptor (GHSR) gene (16).

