## Replacement of individual subjects after withdrawal

Subjects that withdrew from the study prematurely will not be replaced, since a drop-out rate of 10% has been taken into account in the power calculation.

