## Follow-up of subjects withdrawn from treatment

When a subject is withdrawn prematurely from the study, proper follow up will be given if necessary.

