## Univariate analysis

Analyses regarding different treatment and responses between subjects will be executed using ANOVA (with repeated measures), followed by Scheffe’s post-hoc test (when appropriate). Regression analysis (simple/multiple) will be performed for possible correlations between dependent and independent variables.

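### Undefined non-compliance can end a subject's measurements, and the named repeated-measures ANOVA in its classical form drops incomplete subjects: a risk of selection related to outcome and genotype

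*Protocol*

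**What the plan says.** Four parts of the protocol bear on this point.

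- **Leaving the study.** Section 7.4 allows voluntary withdrawal: "Subjects can leave the study at any time for any reason if they wish to do so without any consequences". Section 7.4.1 adds a discretionary route: "In case a subject does not comply with the protocol it also can be decided to exclude that subject from further participation". It gives no definition of non-compliance, no threshold and no decision-maker.
- **After leaving.** Section 7.6 states: "When a subject is withdrawn prematurely from the study, proper follow up will be given if necessary". Its heading concerns withdrawal from treatment but its sentence concerns withdrawal from the study, so stopping the diet and stopping measurement are not kept apart. Section 7.5 adds: "Subjects that withdrew from the study prematurely will not be replaced, since a drop-out rate of 10% has been taken into account".
- **Analysis.** Section 9.2 states: "Analyses regarding different treatment and responses between subjects will be executed using ANOVA (with repeated measures", with a Scheffé post-hoc test and regression.
- **Rationale.** Section 1 reports that "the TA/AA genotype predisposes individuals to a reduced postprandial response in hunger and satiety". A later paragraph of section 1 says that keeping weight off rests largely on psycho-behavioural factors and gives eating behaviour as the example. Section 7.2 makes AA the high-predisposition group and TT the low one, 40 subjects each.

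**The concern.** The objective is to show how genotype groups differ in their response to a maintenance period after weight loss. On the protocol's own account, appetite and eating behaviour lie between genotype and regain. Keeping to a very low energy diet, and to a year of visits, may depend on the same behaviour. Excluding subjects for non-compliance would then condition the AA-TT comparison on something that genotype may affect and that may predict the outcome.

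The main problem is in data collection. If an excluded subject is not measured again, those outcomes do not exist, and no later analysis plan can recover them. The named analysis can add to the loss, because classical repeated-measures ANOVA needs a value at every time point. The visits that such a subject did complete would then also go unused.

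The 10% drop-out allowance does not answer this. It protects the number of subjects but not their comparability.

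**Working it through.** **1. The plan's own figures (section 4.4).** Inputs: REE difference 2068 - 1778 = 290, SD 375, alpha 0.05, power 0.90.

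- 21 × 375² / 290² + 0.96 = 35.11 + 0.96 = 36.07, stated as 36.
- 36 / 0.90 = 40 per group.

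Both reproduce, so the point does not rest on an arithmetic error.

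**2. Loss of numbers.** Two-sided power for a difference of 290 with SD 375:

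| Completers per group | Loss from 40 | Power |
|---|---|---|
| 36 | 10% | 90.7% |
| 32 | 20% | 87.1% |
| 28 | 30% | 82.5% |

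This effect is modest. Selection is the larger issue.

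**3. Selection (all inputs assumed).** The protocol gives no drop-out or non-compliance rate by genotype, so this is an illustration. Let regain Y be normal with SD 1, mean 0 in TT and mean δ in AA, with δ = 0.3, 0.5 or 0.77. Apply one loss rule to both groups:

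logit P(loss) = a + b·Y

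Here b = 0 (no link), 1 or 2 per SD, and a is set so that overall loss is 10%, 20% or 30%. Then compare completers' means.

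| Overall loss | b = 0 | b = 1: share of true difference kept | b = 2: share kept | Shrinkage, b = 1 to 2 |
|---|---|---|---|---|
| 10% | 1.00 | 0.93-0.94 | 0.85 | about 6-15% |
| 20% | 1.00 | 0.89-0.90 | 0.77 | about 10-23% |
| 30% | 1.00 | 0.86-0.87 | 0.71 | about 13-29% |

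These are simulation results. Numerical integration of the same model gives 7-16%, 11-24% and 14-29%, so simulation error is about one percentage point.

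With δ = 0.5 and 10% overall loss, this common rule alone gives 12-13% loss in AA and 7-8% in TT. Unequal loss therefore needs no separate assumption about genotype. It needs only that loss follows regain and that regain differs by group.

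**4. Raw and standardised difference.** Selection also narrows the spread within groups, so the standardised difference shrinks less than the raw one. Example by integration, with δ = 0.5, 10% loss and b = 2: the raw difference is 0.421 and the within-group SD 0.918. Then 0.421 / 0.918 = 0.459, which is 92% of 0.5, while the raw difference is 84% of 0.5.

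**The case against.** **The protocol does not say complete cases.** This is correct. Dropping incomplete subjects is a property of the classical method. Section 7.4.1 stops further participation and does not order deletion of data already collected. An analysis plan that is not shown may define analysis sets and the handling of missing values, so their absence here is not a fault. What stands is that the protocol fixes a removal rule, leaves later measurement unprovided for, and names a method poorly suited to the gaps that follow.

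**A reader might infer that the worst regainers are removed, and more often in AA.** The documents do not support this as fact. Regain is nowhere called non-compliance, and no dietary rule is set for the ten maintenance months. The clearer routes are failing the two-month diet, missing visits, or not completing accelerometer wear or urine collection. A subject who departs from the diet may also lose less and have less to regain. No figure links genotype to compliance. A genotype-related effect is plausible from section 1, but its direction is open.

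**A reader might also infer a bias of a fifth of the planned effect.** Suppose the top 20% of regainers are lost in AA and the top 10% in TT. The means fall by 0.350 and 0.195 SD, a gap of 0.155 SD, against 290 / 375 = 0.773. This fails on three counts. The loss rates are invented. The 0.773 is an REE effect, not a regain effect. Such truncation also cuts the within-group SDs to 0.76 and 0.84 (pooled 0.807), so the standardised difference is (0.773 - 0.155) / 0.807 = 0.766, almost unchanged.

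**Section 7.6 is silent on outcome visits and does not forbid them.** This is true. A sentence providing for them is what is needed.

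**Stopping the diet is a clinical matter.** Agreed. The point concerns measurement only.

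**Conclusion.** The point holds as a risk built into the plan, not as a demonstrated bias. Three provisions act together: discretionary exclusion for undefined non-compliance, no provision for outcome measurement afterwards, and a named analysis that classically discards incomplete subjects. The protocol's own rationale makes loss related to outcome and genotype plausible, and outcomes that were not collected cannot be restored later.

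The size is conditional. If the odds of loss rise with regain as assumed, the raw AA-TT difference among completers shrinks by about 6-15% at 10% overall loss and 13-29% at 30%. It shrinks by nothing if loss is unrelated to regain, and the standardised difference shrinks less than the raw one. These figures apply to an outcome that drives the loss. For energy expenditure, physical activity or fat-cell measures, no bias has been shown. The change is worth making because it is cheap and must be in place before subjects are lost.

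**What to change.** - **Sections 7.4.1 and 7.6.** Reword so that non-compliance with the diet or procedures does not by itself end outcome measurement. Invite such subjects to the remaining visits in Figures 2 and 3. Separate stopping the diet from leaving the study. Whether a subject continues the diet stays a clinical decision, on which nothing is proposed here. Withdrawal of consent and withdrawal for urgent medical reasons are unaffected.
- **Record-keeping.** Log the reason for each exclusion or withdrawal, so that reasons can be tabulated by genotype group.
- **Section 9.2.** Analyse all genotyped subjects who start the programme, in their genotype group. Replace repeated-measures ANOVA with a linear mixed model using all available visits, with genotype, visit and genotype-by-visit terms.
- **Sensitivity analysis.** The mixed model still assumes that missing values are predictable from observed ones. For body weight, add an analysis under data missing not at random, such as shifting unobserved late weights upward by stated amounts and reporting how the AA-TT difference changes.

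The cost is wording in three sections, some attendance at visits that are already planned, and a little more analysis work.

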## Replacement of individual subjects after withdrawal

Subjects that withdrew from the study prematurely will not be replaced, since a drop-out rate of 10% has been taken into account in the power calculation.

## Follow-up of subjects withdrawn from treatment

When a subject is withdrawn prematurely from the study, proper follow up will be given if necessary.

## Premature termination of the study

In case the safety and wellbeing of the subject is in danger, or there are non-expected disadvantages of the participation for the subject, the subject will directly be excluded from the research. There are no risks connected to the premature termination of the study.

In case of premature termination or suspension of the trial for any reason, the investigator will inform:

- The regulatory authorities (MEC)
- The subject, assuring him or her appropriate treatment and follow up

# SAFETY REPORTING

## Section 10 WMO event

In accordance to section 10, subsection 1, of the MRA, the investigator will inform the subjects and the reviewing accredited MEC if anything occurs, on the basis of which it appears that the disadvantages of participation may be significantly greater than was foreseen in the research proposal. The study will be suspended pending further review by the accredited MEC, except insofar as suspension would jeopardize the subjects’ health. The investigator will take care that all subjects are kept informed.

## Adverse and serious adverse events

Adverse events are defined as any undesirable experience occurring to a subject during a clinical trial, whether or not considered related to the investigational product. All adverse events reported spontaneously by the subject or observed by the investigator will be recorded.

A serious adverse event is any untoward medial occurrence or effect that at any dose results in death;

- is life threatening (at the time of the event);
- requires hospitalization or prolongation of existing inpatients’ hospitalization;
- results in persistent or significant disability or incapacity
- is a congenital anomaly or birth defect;
- is a new event of the trial likely to affect the safety of the subjects, such as an unexpected outcome of an adverse reaction, lack of efficacy of an IMP used for the treatment of a life threatening disease, major safety finding from a newly completed animal study, etc.

Al serious adverse events will be reported to the accredited MEC that approved the protocol, according to the requirements of that MEC.

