*Nature and extent of the burden and risks associated with participation, benefit and group relatedness:* All subjects visit the university six times. The time burden for each subject depends on whether they belong to the high or low predisposition group or not. For all subjects there is a screening of around 45 minutes. Four visits for the group with medium predispositio, and therefore limited measurements (body weight, waist and hip circumference and body composition), will take 60 minutes and one visit of 20 minutes. In total these subjects need to stay at the university for approximately 305 minutes (=5h). Three visits for the subjects in the groups with a high/low predisposition for weight regain will take one night and the subsequent morning, so approximately 16h. The other two visits will be 20 and 60 minutes. In total these subjects need to stay at the university for approximately 50h. There are no risks for the subjects in consuming the VLED (Modifast, together with the recommended fruit and vegetables) as the macronutrient composition and vitamins/minerals content meet the Dutch recommended daily allowance. This VLED will demand some energy from the subjects at home. However, losing weight is a great advantage for these subjects, so probably they have enough will-power to complete these 2 months VLED. There is a risk of minor bruising during blood sampling. Deuterium is an isotope of water that naturally appears in the body. Drinking it does not expose the subject to any risks. The doubly labelled water is safe to use in humans since the water is labelled with stable isotopes. The concentrations of the samples are with an enrichment of 100 to 200 ppm far below 10000 ppm or 1%, where effects on biological systems have been observed. Collection of urine at home is only a minor time burden for the subjects. Studies in the respiratory chamber will be conducted using standard operating procedures. A pair of subjects will always participate in the study at the same time and therefore they will never be alone. The subjects will be able to contact the investigators during the entire night. In addition, they will be able to get out of the chamber at any time they feel uncomfortable. Taking a fat biopsy will be done under local anaesthetic, which only gives a very brief tingling pain at the site of infiltration under the skin. Local anaesthesia occurs with most standard clinical procedures in which this is used, resulting in minimal risks. Allergies for local anaesthetics will be one of the exclusion criteria. The biopsy itself can give a mild soreness and bruising near the biopsy site. Minimal scarring rarely occurs. Wearing the Tracmor will not have any risk and only minor time burden.

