# STUDY DESIGN

Subjects screened for participation

Subjects excluded because they did not met inclusion criteria

Subjects included follow weight loss program

2 months (n = 200)

Highest predisposition for weight regain-group (n = 40)

 All measurements

Lowest predisposition for weight regain-group (n = 40)

 All measurements

Weight maintenance period of 10 months

Medium predisposition for weight regain (n = 120)  limited measurements

Fig 1. Flow of participants through the study

Subjects will be assigned to a subgroup based on their genetic profile, which will be determined with genotyping analysis from the blood drawn during the screening (for detail see section 7.3). The three groups will consist of subjects with a high predisposition for weight-regain, a low predisposition for weight regain and all subjects in between. All subjects undergo a weight loss program, followed by a weight maintenance period. The subjects in the group of low and high predisposition for weight regain will be studied more thoroughly, while the others will only undergo the more basal measurements. Figure 2 and 3 give an overview of all the measurements that will be done in the groups with a high/low predisposition for weight regain and the group with medium predisposition respectively (for details of the measurements see section 7.3).

|  | **Screening** | **Pre-weight loss** | **Weight reduction program (2 months)** | **Post-weight loss** | **Weight maintenance program (10 months)** | **Post-weight maintenance** |
| --- | --- | --- | --- | --- | --- | --- |
| Measurements |  | Month 0 | Months 1 | Month 2 | 3 months after start maintenance | 10 months after start maintenance |
| **Body weight**  **Height**  **Body mass index**  **Waist/Hip** | X  X  X  X | X  X  X | X  X  X | X  X  X | X  X  X | X  X  X |
| **TFEQ**  **Baecke** | X  X | X  X | X  X | X  X | X  X | X  X |
| **Total Body Water**  **Body density** |  | X  X |  | X  X | X  X | X  X |
| **SMR**  **BMR** |  | X  X |  | X  X |  | X  X |
| **Physical activity** |  | X |  | X | X | X |
| **Doubly labelled water** |  | X |  | X |  | X |
| **Blood parameters**  **Polymorphisms** | X  X |  |  |  |  |  |
| **Adipocytes** |  | X |  | X |  | X |
| **Time** | 45 min | 16h | 20 min | 16h | 60 min | 16h |

Fig 2. Measurements for the group with a high and low predisposition for weight regain. Three Factor Eating Questionnaire (TFEQ), Sleeping metabolic rate (SMR), basal metabolic rate (BMR).

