# METHODS

## Study parameters/endpoints

### Main study parameter/endpoint

The role of the genetic background involved in weight regain through mechanisms including energy expenditure, physical activity and adipogenic capacity.

Energy expenditure (see fig 2, page 13, and page 21 and 22 for detailed description) will be determined via three measurements. First, the respiration chamber measurements, which will determine oxygen consumption and carbon dioxide production overnight to determine sleeping metabolic rate. Second, the ventilated hood measurements in the mornings to determine basal metabolic rate. And the last measurement is the use of doubly labelled water to determine total energy expenditure. These measurements will be performed before and after weight loss, and after weight maintenance.

Physical activity (see fig 2+3 on page 13+14, and page 20 for detailed description) will be determined via a triaxial accelerometer, which ensures movement registration sensitive to a wide range of body movements, thereby determining habitual physical activity. These measurements will be performed before and after weight loss, and after weight maintenance.

Adipogenic capacity (see fig 2, page 13, and page 21 for detailed description) will be determined via measurements on number and size of fat cells from fat biopsies. These measurements will be performed before and after weight loss, and after weight maintenance.

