Oxygen consumption and carbon dioxide production will be measured in the respiration chamber. The respiration chamber is a 14m3 hotel room, furnished with a bed, chair, computer, television, radio, dvd-player, telephone, intercom, sink and toilet. The room is ventilated with fresh air at a rate of 70-80 l/min. The ventilation rate is measured with a dry gas meter. The concentrations of oxygen and carbon dioxide will be measured using a paramagnetic O2 analyzer and an infrared CO2 analyzer. During each 15-min period six samples of outgoing air for each chamber, and one sample of fresh air, zero gas, and calibration gas will be measured. The gas samples to be measured will be selected by a computer that also stores and processes the data. Metabolic rate is calculated using Weir’s formula (41).

Sleeping metabolic rate

Sleeping metabolic rate (SMR) is defined as the mean metabolic rate during three consecutive hours between 00:00h and 07:00h with most stable energy expenditure.

Basal metabolic rate

The following morning when leaving the respiration chamber in a fasted state, the subjects go immediately under a ventilated hood to measure basal metabolic rate. After 15 min resting, basal metabolic rate will be measured by means of an open circuit ventilated hood system with subjects lying supine for 30 min (42). Gas analysis is performed by a paramagnetic oxygen analyzer (omnical type 1155B, Crowborough Sussex, UK) and an infrared carbon dioxide analyzer (omnical type 1520/1507).

After the ventilated hood measurement the subjects’ body composition will be determined and a fat biopsy will be taken as described above. After all these measurements the subjects will receive a breakfast before they are sent home. The subjects will be able to choose from several food items, unless they are in the weight loss program where they only receive the VLED (Modifast). All foods will be prepared in a research kitchen from the Department of Human Biology by one of the researchers.

Total energy expenditure

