## Benefits and risks assessment, group relatedness

Subjects can have an advantage of the study, namely that they might lose some weight. However, there are some risks regarding blood sampling, but they will be kept as minimal as possible, due to appropriate hygiene precautions. Subjects will be informed about the risks like minor bruising. Furthermore, deuterium is an isotope of water that naturally appears in the body. Drinking it does not expose the subject to any risks. The doubly labelled water is safe to use in humans since the water is labelled with stable isotopes. The concentrations of the samples are far below 10000 ppm or 1%, where effects on biological systems have been observed. There are no risks for the subjects in consuming the VLED (Modifast, together with the recommended fruit and vegetables) as the macronutrient composition and vitamins/minerals content meet the Dutch recommended daily allowance. Moreover, all subjects will be properly instructed and can call/mail anytime for question concerning their diet. Taking a fat biopsy will be done under local anaesthetic, which only gives a very brief tingling pain at the site of infiltration under the skin. Local anaesthesia occurs with most standard clinical procedures in which this is used, resulting in minimal risks. Allergies for local anaesthetics will be one of the exclusion criteria. The biopsy itself can give a mild soreness and bruising near the biopsy site. Minimal scarring rarely occurs. Wearing the TracmorD will not have any risk or burden. Studies in the respiratory chamber will be conducted using standard operating procedures. A pair of subjects will always participate in the study at the same time and therefore they will never be alone. The subjects will be able to access the investigators during the entire night. In addition, they will be able to get out of the chamber at any time they feel uncomfortable.

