## End of study report

The investigator will notify the accredited METC of the end of the study within a period of 8 weeks. The end of the study is defined as the last patient’s last visit.

In case the study is ended prematurely, the investigator will notify the accredited METC, including the reasons for the premature termination.

Within one year after the end of the study, the investigator/sponsor will submit a final study report with the results of the study, including any publications/abstracts of the study, to the accredited METC.

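### Adverse events are recorded only when volunteered or observed, and no scheduled contact is stated after the third fat biopsy, so events appearing after discharge are likely to be under-recorded

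*Protocol*

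**What the plan says.** Section 8.2 defines an adverse event broadly, then gives the recording rule: "All adverse events reported spontaneously by the subject or observed by the investigator will be recorded". Nowhere does the protocol describe a question put to subjects at visits, a diary or a safety call.

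The biopsies are the most invasive procedure in the study. Of the adipocyte measurements, section 7.1.1 says "These measurements will be performed before and after weight loss, and after weight maintenance". Fig 2 in section 3 marks them at month 0, month 2 and 10 months after the start of maintenance, which is its last column. The Summary states "All subjects visit the university six times", counting screening.

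Within each of these visits, section 7.3 puts the biopsy after the ventilated hood measurement, near the end of the morning: "After all these measurements the subjects will receive a breakfast before they are sent home". Section 10.4 names the expected harms: "The biopsy itself can give a mild soreness and bruising near the biopsy site. Minimal scarring rarely occurs". The Summary says the same.

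Section 8.3 follows adverse events until they resolve or stabilise. Section 8.2.2 commits the sponsor to an annual report that includes a full safety analysis. Section 11.4 says "The end of the study is defined as the last patient’s last visit".

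**The concern.** A rule that waits for events to be volunteered or seen works best when subject and investigator meet soon after the exposure. Here they do not. The subject leaves shortly after the biopsy, the next scheduled visit is weeks or months away, and after the third biopsy none is stated. Even at the visits that do follow, nobody is required to ask. Section 8.3 does not help, because it applies only to an event already known.

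What is at stake is the completeness of the safety record for a research procedure, and so the basis of the safety analysis in section 8.2.2. Safety is not a study endpoint, so no efficacy or mechanistic conclusion depends on it.

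**Working it through.** **Number of biopsied subjects.** Section 4.4 gives N = 21 × SD² / (difference)² + 0.96, with SD 375 and means 2068 and 1778:

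- 21 × 375² / 290² + 0.96 = 2,953,125 / 84,100 + 0.96 = 35.11 + 0.96 = 36.07, which reproduces the stated 36.
- 36 / 0.90 = 40 per group, as stated. Two groups give 80 subjects.

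**No unlisted later visit.** For the high and low groups, Fig 2 gives 45 min + 3 × 16 h + 20 min + 60 min = 45 + 2,880 + 20 + 60 = 3,005 min = 50.1 h. The Summary states about 50 h. The time budget therefore contains no visit after the third overnight stay.

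**Interval from each biopsy to the next scheduled visit** (Fig 2, taking maintenance to start at month 2):

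| Biopsy | When | Next scheduled visit | Gap |
| --- | --- | --- | --- |
| 1 | month 0 | month 1 | about 1 month |
| 2 | month 2 | 3 months after start of maintenance | about 3 months |
| 3 | 10 months after start of maintenance | none stated | – |

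**Share with no later scheduled visit.**

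- As planned: 80 × 3 = 240 biopsies, of which 80 are third biopsies; 80 / 240 = 33.3%.
- With 10% drop-out, 72 third biopsies remain. The total depends on when the 8 subjects leave, which the protocol does not say:
  - between biopsies 2 and 3: 80 + 80 + 72 = 232, share 72 / 232 = 31.0%;
  - between biopsies 1 and 2: 80 + 72 + 72 = 224, share 72 / 224 = 32.1%;
  - before biopsy 1: 3 × 72 = 216, share 72 / 216 = 33.3%.

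The share is about one third in every case.

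**Other possible contacts.** Section 7.3 has the accelerometer worn for two weeks at the start of weight loss, at the start of maintenance and at the end of the experiment. Doubly labelled water needs urine samples over 14 days. Handing these in may bring subject and staff together. However, the protocol does not say when or how items are returned, does not place the last return after the last biopsy, and attaches no adverse-event question to it. Section 10.4 offers calls or mail at any time, but for questions about the diet.

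**The case against.** The other side has real points, and they limit what can be claimed.

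- **The rule does not forbid asking.** Section 8.2 says what will be recorded and does not bar an enquiry. That stands. But asking is not planned, so it cannot be relied on or assumed uniform across visits and groups.
- **The timing of the harms is not stated.** The protocol names soreness, bruising and rare scarring without saying when they appear. Some may be seen before discharge. Under-recording is therefore likely, not demonstrated.
- **Study end.** A reader might infer that collection closes at each subject's own final visit. Section 11.4 sets a single study-level date, the last visit of the last patient. For nearly everyone the study is still open after their third biopsy, and a spontaneous report can be recorded. Only a scheduled contact is missing.
- **The suspension trigger.** A reader might infer that section 8.1 is blinded. It turns on evidence that "the disadvantages of participation may be significantly greater than was foreseen in the research proposal". Mild soreness, bruising and rare scarring are foreseen, so missing some of them does not disable that trigger. Likewise, the listed counts in the annual report are of serious reactions; the exposed part is its general safety analysis.
- **Complication-rate bounds.** A reader might compare zero-event one-sided 95% upper bounds of 1 − 0.05^(1/160) = 1.85% and 1 − 0.05^(1/240) = 1.24%. This treats the first 160 biopsies as fully ascertained, which a passive rule does not deliver. It also assumes no events where the protocol expects some, and the protocol has no complication-rate objective.
- **Group comparison.** A reader might infer bias from about 50 h on site against about 5 h in the medium group. No comparison of adverse events between groups is planned, all subjects have six visits, and exposure to the procedures differs by design.

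**Conclusion.** The point holds as a modest gap in safety collection. Capture is passive throughout, and about one third of biopsies (80 of 240 planned, or about 72 after drop-out) have no stated scheduled contact afterwards. The other two thirds are followed by a visit only after about 1 or 3 months, again with no planned question. Events that emerge after discharge are likely to be under-recorded, which weakens the safety analysis of section 8.2.2.

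This rests on two assumptions: that at least some biopsy effects appear or persist after the subject has gone home, and that return of the final urine samples or accelerometer is not already used as a safety contact. The extent of under-recording cannot be calculated from the protocol. The named harms are mild, and neither the sample size nor the primary analysis is affected.

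**What to change.** Amend section 8.2 so that one standard open adverse-event question is asked at every scheduled visit in all three groups, in addition to recording spontaneous and observed events.

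Add one brief enquiry after the final biopsy. Make it when the 14-day urine samples are returned, if that falls after the biopsy, and otherwise by a short call. State that each subject's adverse-event collection runs to that contact.

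The cost is a few minutes per existing visit and one short contact for each of up to 80 subjects. Recorded event counts will be somewhat higher; any report should say that events were asked for, so that the rise is not read as worse tolerability.
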